#### Ventilatory management

In the HFNC group, the initial gas flow setting will be 6 L/min for all infants. The fraction of inspired oxygen (FiO_2_) will be adjusted to maintain pulse oximetry oxygen saturation (SpO_2_) between 90–94%, and the maximum FiO_2_ will be increased up to 0.40 to ensure adequate oxygenation. According to the SpO_2_ and arterial partial pressure of carbon dioxide (PaCO_2_) levels, the gas flow can be increased up to a maximum of 8 L/min.

In the CPAP group, the initial CPAP setting will be 6 cmH_2_O for all infants. FiO_2_ will be adjusted to maintain SpO_2_ between 90–94%. If necessary, the maximum FiO_2_ will be increased up to 0.40 to ensure adequate oxygenation. According to the SpO_2_ and PaCO_2_ levels, the CPAP can be increased up to a maximum of 8 cmH_2_O to optimize respiratory support and maintain appropriate oxygenation and ventilation.

In the NIPPV group, the starting parameters of ventilator will be set as follows:❿ Positive end-expiratory pressure of 6 cmH_2_O (can be increased up to 8 cmH_2_O, according to the SpO_2_ levels);❿ Peak inspiratory pressure (PIP) of 10–15 cmH_2_O (can be increased up to 25 cmH_2_O, according to the SpO_2_ and PaCO_2_ levels);❿ Inspiratory time (IT) of 0.5 s (can be adjusted ranging from 0.4–0.6 s), and rate will be 30 breaths per minute (bpm) (can be increased up to 60 bpm, according to PaCO_2_ levels);❿ FiO_2_ will be adjusted to maintain SpO_2_ between 90–94%, and the maximum FiO_2_ is 0.40.

#### Weaning from study interventions

The assigned intervention will be weaned based on the clinical assessment of infants and the following protocol:In HFNC group, the gas flow for infants can be decreased down to 2 L/min;In CPAP group, the setting pressure for infants can be decreased down to 4 cmH_2_O;In NIPPV group, the PIP and PEEP for infants can be decreased down to 8 cmH2O and 4 cmH_2_O respectively. The rate can be decreased down to 20 bpm.

The study intervention will be stopped when the parameters are reduced to the above and can maintain for at least 24 h with the following:

FiO_2_ ≤ 0.25;SAS < 3;No apnea that cannot be self-recovered.

If infants need FiO_2_ > 0.25 to maintain SpO_2_ at 90–94%, SAS > 3 points, or have apnea ≥ 1 time a day that cannot be self-recovered, the assigned intervention will be continued and reassessed after at least 24 h. After weaning of the intervention, neonates can receive continuous hood oxygen therapy, or low-flow oxygen therapy via nasal cannula, if needed. If reintroduction of NIV is required within 48 h after weaning, the previously assigned intervention will be used.

Pulmonary surfactant (Curosurf®) will be administered to infants with FiO_2_ > 0.30 and with RD syndrome (RDS) on chest x-ray or ultrasound [33]. A dose of 200 mg/kg will be administered by INSURE (intubation-surfactant-extubation) method. If the infant’s RD persists and FiO_2_ remains > 0.30 for 6–12 h after the first dose, an additional dose of 100 mg/kg will be given. PaCO_2_ will be monitored by blood gas analysis [38] or transcutaneous monitoring [39] according to local policy. SpO2, electrocardiogram (ECG), heart rate will be continuously monitored by bedside monitors. To relieve abdominal distension, each patient will be placed with an orogastric tube, through which gas can be aspirated according to nurses’ assessment.

### Criteria for discontinuing or modifying allocated interventions {11b}

The assigned interventions may be terminated or modified under the following circumstances:Treatment failure criteria: If an infant meet any of the predefined treatment failure criteria, the assigned intervention will be terminated. These criteria may include specific clinical parameters or worsening of the infant’s condition that indicate the need for a different level of respiratory support or intervention;Guardian request: If the guardian of an enrolled infant requests the termination of the assigned intervention, their decision will be respected, and appropriate actions will be taken based on the infant’s clinical condition;Principal investigator’s decision: The principal investigator, who is responsible for the overall conduct of the study, may deem it necessary to terminate or modify the assigned intervention. This could be due to safety concerns for the subjects or other relevant factors that warrant a change in the treatment approach;Ethics committee determination: If the ethics committee overseeing the study determines that there are significant safety issues or other ethical concerns that warrant the termination of the trial, they may recommend discontinuing the assigned interventions.

### Strategies to improve adherence to interventions {11c}

Before commencing the study, the principal investigator and team members will convene a meeting to review the study protocol, data collection and management procedures, and specific intervention details.

After discussion, we have decided to make the following modifications. Due to not all relevant healthcare personnel participating in the study being proficient in all modes of respiratory support, and the management and operation of respiratory support being crucial for the success of this trial, it was decided through discussion that training is necessary. The protocol manuscript has been distributed to the relevant personnel at the participating centers 45 days prior to recruitment. The principal investigator has conducted online meetings to explain the study protocol to all researchers, with a focus on intervention details. A dedicated discussion group has been established on a social media platform to facilitate prompt answering of any questions. Respiratory therapists who are skilled and knowledgeable about the protocol and principles have been assigned to each center to provide practical training on operational procedures and address related queries. Two weeks prior to the commencement of recruitment, all personnel involved in respiratory support operations and management were proficient in performing the relevant procedures according to the protocol.

To ensure the smooth implementation of the protocol as per requirements, the principal investigator will regularly supervise and assess the performance of healthcare personnel. Regular online summary meetings will be conducted to review any issues and challenges encountered during the trial period and to identify ways for improvement and solutions.

### Relevant concomitant care permitted or prohibited during the trial {11d}

All neonates including in the trial will receive standard supportive care such as blood tests, X-rays, antibiotics use, parenteral and enteral nutrition according to local policy.

### Provisions for post-trial care {30}

Not applicable. The interventions involved in this trial have minimal harm, and after the trial, the subjects will receive standard care according to local policies.

### Outcomes {12}

#### Primary outcome

The primary outcome is treatment failure within 72 h after randomization [34]. Treatment failure is defined as meeting one or more of the following criteria when the neonate has received maximal therapy for the assigned treatment:Sustained increase in oxygen requirement: FiO_2_ > 0.40 to maintain SpO_2_ of 90%-94% for more than one hour.Respiratory acidosis: potential of Hydrogen (pH) ≤ 7.20 and PaCO_2_ > 60 mm Hg.Frequent or severe apnea despite drug therapy or respiratory support: two or more apnea events requiring bag-mask ventilation within 24 h, or three or more apnea events requiring intervention (stimulation, increasing oxygen or ventilation pressure) within one hour.Emergency situations such as pulmonary hemorrhage, pneumothorax, heart failure, shock, etc., require endotracheal intubation, or it may be deemed necessary by the pediatrician.

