## Assignment of interventions: blinding

### Who will be blinded {17a}

In this trial, blinding of the healthcare professionals involved in delivering the respiratory support methods (doctors, nurses, and respiratory therapists) is not feasible due to the nature of the intervention; it is meaningless to blind the infants. To minimize risk of bias, we developed objective criteria for the primary outcome. Outcome assessors and data analysts will be blinded to the treatment allocation and not involved in the treatment process.

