## Discussion

Innovation of this study: Currently, evidence for the use of NIPPV in neonates with GA ≥ 32 weeks is still insufficient. This study will supplement the data on the application of NIPPV in neonates with GA ≥ 32 weeks and compare the effectiveness and safety of the three most used modes in the NICU: CPAP, NIPPV, and HFNC. This will provide more evidence for clinical application of NIV in this population.

Limitations of this study: 1) Blinding of the healthcare professionals involved in the diagnosis and treatment of the neonates is not feasible due to the nature of the ventilation mode being used in the study. However, to minimize potential bias, objective primary outcome criteria have been established. These criteria will be used to assess the outcomes in a standardized and unbiased manner, reducing the impact of lack of blinding on the study results. 2) In this trial, the term “NIPPV” includes both traditional NIPPV and BiPAP. BiPAP is commonly categorized as a form of NIPPV [35]. Previous studies have indicated that both traditional NIPPV and BiPAP show comparable efficacy in preventing treatment failure and the need for MV [51]. Therefore, traditional NIPPV and BiPAP can be considered interchangeable in terms of their effectiveness. Considering that the maximum pressure of BiPAP is lower, traditional NIPPV can be used when the required pressure exceeds the upper limit of BiPAP.

Our study aims to generate robust clinical evidence regarding the efficacy and safety of noninvasive respiratory support in neonates with GA ≥ 32 weeks, and strive to minimize tracheal intubation and mechanical ventilation, and reduce complications related to NIV.

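### As worded, the primary outcome omits emergency intubations before maximal settings, and its fourth criterion admits unblinded judgement, so the objectivity claim holds only for the first three criteria

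*Protocol article*

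**What the plan says.** In the protocol article, the Primary outcome section fixes the window ("The primary outcome is treatment failure within 72 h after randomization") and then gives one lead-in for the whole list: "Treatment failure is defined as meeting one or more of the following criteria when the neonate has received maximal therapy for the assigned treatment". Four criteria follow:

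1. A sustained oxygen requirement, with an FiO2 threshold and a duration.
2. Respiratory acidosis, with pH and PaCO2 thresholds.
3. Apnea, with event counts per period.
4. Intubation: "Emergency situations such as pulmonary hemorrhage, pneumothorax, heart failure, shock, etc., require endotracheal intubation, or it may be deemed necessary by the pediatrician".

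On bias, the section Who will be blinded {17a} says that doctors, nurses and respiratory therapists cannot be blinded and names the safeguard: "To minimize risk of bias, we developed objective criteria for the primary outcome". The limitations paragraph of the Discussion repeats it: "objective primary outcome criteria have been established". Outcome assessors and data analysts are to be blinded.

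Three other sections matter. Objectives {7} states the aim as reducing the need for invasive ventilation. Ventilatory management gives the starting and maximal settings in each arm. Criteria for discontinuing or modifying allocated interventions {11b} makes meeting any failure criterion a reason to end the assigned support.

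**The concern.** Two features of the same definition cause trouble.

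**Events that may go uncounted.** The maximal-therapy condition governs the whole list. Pneumothorax, pulmonary hemorrhage and shock can arise at any setting. If one of them leads to intubation while the infant is still below the arm's maximum, the wording does not make that infant a primary-outcome event. Two careful assessors could classify the same infant differently.

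**Events that rest on judgement.** Criterion 4 is an open list that closes with "require endotracheal intubation, or it may be deemed necessary by the pediatrician". No threshold is attached, and the person deciding knows the allocation. A blinded assessor can only record that decision after it has been made. The safeguard that the protocol offers against lack of blinding therefore does not reach this part of the outcome.

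At stake are the power of the primary comparison if real failures are lost, and its false-positive rate if discretion is used more readily in one arm than another.

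**Working it through.** **Step 1. Does the condition reach criterion 4?** The lead-in comes before the list, and criterion 4 is an item in that list. It contains no phrase such as *regardless of settings*. Nothing elsewhere in the article supplies an exception. Against Objectives {7}, which is about the need for invasive ventilation, omitting early emergency intubations would drop events of the kind the trial sets out to reduce.

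**Step 2. How far does the objectivity claim extend?** Criteria 1–3 each carry numerical thresholds or counts. Criterion 4 has none for the pediatrician's decision. The claim in {17a} and the Discussion is supported for three criteria of four.

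**Step 3. The plan's own figure.** Inputs from Sample size {14}: HFNC 20.5%, CPAP 10.2%, alpha 0.0167, power 0.80. The two-tailed test is from Statistical methods {20a}.

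n = (z₁₋α/₂ + z₁₋β)² × [p₁(1−p₁) + p₂(1−p₂)] / (p₁−p₂)²

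= (2.3932 + 0.8416)² × (0.162975 + 0.091596) / 0.103² = 10.4644 × 0.254571 / 0.010609 = 251.1, so **252 per arm**.

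The plan's figure is reproduced, and this point does not question it. With a pooled-variance test, power at 252 per arm is 0.795. That is the baseline below.

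**Step 4. Illustration: discretionary excess in one arm.** Assume two arms that both have 10.2% true failure, 252 infants each, and x points added in one arm by discretion. The documents give no value for x, so a range is shown. With a = 0.102 + x, b = 0.102, p̄ = (a+b)/2, SE₀ = √(2p̄(1−p̄)/252), SE₁ = √([a(1−a)+b(1−b)]/252) and c = 2.3932 × SE₀:

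rejection rate = 1 − Φ((c−x)/SE₁) + Φ((−c−x)/SE₁)

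Worked for x = 0.03: SE₀ = 0.02863, c = 0.06853, SE₁ = 0.02860, (c−x)/SE₁ = 1.347, rate = 0.089.

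| Excess in one arm | False-positive rate |
|---|---|
| 0 points | 1.67% |
| 1 point | 2.4% |
| 2 points | 4.7% |
| 3 points | 8.9% |
| 5 points | 23.9% |

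**Step 5. Illustration: failures uncounted equally in both arms.** Assume a share f of failures occurs before maximal settings and is lost in both arms. The documents give no value for f. The observed rates become 20.5%×(1−f) and 10.2%×(1−f). The same rejection formula applies, with the difference in observed rates in place of x.

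| f | Observed rates | Power at 252 per arm |
|---|---|---|
| 0 | 20.5% vs 10.2% | 0.795 |
| 5% | 19.5% vs 9.7% | 0.77 |
| 10% | 18.5% vs 9.2% | 0.74 |
| 20% | 16.4% vs 8.2% | 0.67 |
| 30% | 14.4% vs 7.1% | 0.59 |

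**The case against.** **The literal reading is too strict.** Criterion 4 names sudden events for which stepwise escalation makes little sense, so the authors may well have intended it to stand alone. That is plausible, and for this reason the point concerns wording and is not proof that events will be lost. But the text does not state that intention, and a primary outcome should not depend on assessors guessing it.

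**The objectivity claim is modest.** Three criteria carry numbers, and the Discussion lists lack of blinding as a limitation whose impact is only reduced. This stands as far as it goes. It does not cover the discretionary clause.

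**Bias in favour of NIPPV.** A reader might infer that the condition suppresses failures mainly under NIPPV, because Ventilatory management gives that arm several adjustable settings (PIP, PEEP and rate) against one for CPAP and one for HFNC, apart from FiO2. The documents do not support this as a conclusion. They give no share of emergencies before maximal settings in any arm. Having more settings to raise is arguably part of the strategy under test. Equal lost shares in arms with equal true failure would create no spurious difference.

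**INSURE as failure.** Surfactant "will be administered by INSURE (intubation-surfactant-extubation) method", and a reader might infer that these intubations fall under criterion 4. That reading is strained: the procedure is protocol-specified, its trigger (FiO2 above 0.30) lies below the failure threshold (above 0.40), it ends in extubation by definition, and surfactant treatment is a separate secondary outcome. A clarifying note would be optional.

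**Detail left to other documents.** An article need not show the case report form or every sensitivity analysis, and their absence is not criticised here. The point rests on wording that the article does state.

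**Conclusion.** The point holds as a defect in the definition of the primary outcome. As written, an emergency intubation within 72 h but before maximal settings does not count, which sits badly with the trial's stated aim. Failure can also rest on an unblinded pediatrician's judgement alone, so the claim of objective criteria is correct only for criteria 1–3.

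The direction and size of any bias between arms cannot be determined from the documents. The figures are conditional illustrations: the false-positive rate rises from 1.67% to between 2.4% and 23.9% for an assumed excess of 1 to 5 points in one arm, and power falls from about 0.79 to between 0.77 and 0.59 for an assumed 5% to 30% of failures uncounted equally. Small departures do little harm; the upper ends would matter.

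**What to change.** For outcome classification only:

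- State that the maximal-therapy condition applies to criteria 1–3, and that every emergency intubation within 72 h of randomization counts as failure whatever the settings at the time.
- Pre-specify a sensitivity analysis of the primary outcome, based on the recorded triggering criterion, in which failures resting only on the pediatrician's judgement are not counted and the infants stay in the denominator. It shows how far the result depends on discretion. It cannot show whether those infants would later have met criteria 1–3.
- In {17a} and the Discussion, limit the objectivity statement to criteria 1–3.
- Reconcile the Primary outcome section with {11b}, which uses the same criteria to end the assigned support, so that the change in classification sets no rule for care.

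**Cost.** Trial status gives a recruitment start of September 1, 2023 and an estimated completion of August 31, 2025, so this would be an amendment during recruitment. Section {25} requires notice to the ethics committee and a registry update for revisions that affect evaluation of the results. Infants already enrolled would need reclassifying from recorded intubations. The planning rates come from the study that the article also cites for its outcome, so the sponsor should check that they still suit the clarified definition.

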### Objectives {7}

The objective of this study is to compare the clinical effectiveness of HFNC, CPAP, and NIPPV as primary respiratory support in neonates with RD who are ≥ 32 weeks GA in reducing the need for IMV. We hypothesize that NIPPV is more effective than CPAP and HFNC in preventing treatment failure in neonates ≥ 32 weeks GA.

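### As worded, the maximal-therapy condition also governs emergency intubation, so an infant intubated in an emergency below the ceiling settings may not be scored as a treatment failure

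*Protocol article*

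**What the plan says.** Protocol article, Primary outcome: the outcome is treatment failure within 72 h of randomization. The list of criteria is introduced by "Treatment failure is defined as meeting one or more of the following criteria when the neonate has received maximal therapy for the assigned treatment". The criteria are a sustained oxygen requirement, respiratory acidosis, frequent or severe apnea, and fourthly "Emergency situations such as pulmonary hemorrhage, pneumothorax, heart failure, shock, etc., require endotracheal intubation, or it may be deemed necessary by the pediatrician".

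Ventilatory management gives each mode a starting value and a maximum. For CPAP, "the initial CPAP setting will be 6 cmH_2_O for all infants" and "the CPAP can be increased up to a maximum of 8 cmH_2_O". The other two modes follow the same pattern.

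Objectives {7} states that the three modes are to be compared "in reducing the need for IMV". The section on discontinuing or modifying allocated interventions {11b} says: "If an infant meet any of the predefined treatment failure criteria, the assigned intervention will be terminated". It does not repeat the maximal-therapy condition.

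**The concern.** The condition suits a gradual deterioration. It stops an infant being called a failure on oxygen or carbon dioxide while the assigned mode still has room to be increased. It does not suit an emergency. Nothing in the protocol requires an infant in shock or with a pulmonary hemorrhage to be taken to the ceiling settings before intubation.

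Because the condition stands ahead of the whole list, an emergency intubation below the ceilings fails the definition as written, and the infant becomes a non-failure on the primary outcome. The treating staff are unblinded. Under Who will be blinded {17a}, the outcome assessors are blinded and take no part in treatment, and the protocol relies on objective criteria to limit bias. For this event the wording and the apparent intent give opposite scores, so the criteria do not settle it.

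**Working it through.** The point rests on the text and not on a calculation, so the places are set side by side.

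**1. Does the condition reach the fourth criterion?** It is part of the sentence that introduces the list, and all four criteria depend on that sentence. No other section lifts it for any of them.

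**2. Can an infant be intubated below the ceilings?** Maximal therapy is undefined; it is taken here as the maxima under Ventilatory management.

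| Arm | Start | Maximum |
|---|---|---|
| HFNC | 6 L/min | 8 L/min |
| CPAP | 6 cmH2O | 8 cmH2O |
| NIPPV, PEEP | 6 cmH2O | 8 cmH2O |
| NIPPV, PIP | 10–15 cmH2O | 25 cmH2O |

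Every arm starts below its maximum, and the weaning rules allow lower settings still (2 L/min; 4 cmH2O; PIP 8 with PEEP 4 cmH2O). An emergency can therefore occur below the ceiling in any arm.

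**3. Does this fit the rest of the protocol?**
- *Objective.* An infant who needed invasive ventilation would be a success in a trial that aims to reduce that need.
- *Stopping rule {11b}.* If the section uses the criteria without the condition, the same intubation is a failure at the bedside and a non-failure in scoring. If it carries the condition over, an infant already intubated has not met the failure rule for ending the assigned mode.
- *Secondary outcomes.* Known air leak is excluded at entry, so a pneumothorax under the fourth criterion is first recognised after entry. Air leak is a secondary outcome with no settings condition. The same infant could be an air-leak event, be intubated, and still be a primary-outcome success. Duration of invasive ventilation is listed, but intubation within 72 h as an event is not.

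**4. Scale.** The planned arm size reproduces with an unpooled two-proportion formula at 20.5% vs 10.2%, two-sided alpha 0.0167 and power 0.80:

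n = (2.393 + 0.842)² × (0.205 × 0.795 + 0.102 × 0.898) / 0.103² = 10.465 × 0.25457 / 0.010609 ≈ 251.1, rounded up to 252.

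One re-scored infant in an arm of 252:
- 1/252 = 0.40 percentage points on the failure rate.
- Expected failures at 20.5%: 252 × 0.205 = 51.7; one infant is 1/51.7 = 1.9% of them.
- Expected failures at 10.2%: 252 × 0.102 = 25.7; one infant is 1/25.7 = 3.9% of them.

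These figures hold for any re-scored infant. They do not estimate how many there will be.

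**The case against.** The strongest reply is that nobody would score the outcome this way. Increases are tied to SpO2 and PaCO2, so maximal therapy could mean the most that was indicated for that infant. On that reading an infant intubated for a hemorrhage at 6 cmH2O had received maximal therapy and counts as a failure. Demanding the ceilings first would also empty much of the fourth criterion, and {11b} is written without the condition. Data assessors are to be trained on the protocol (Plans for assessment and collection of outcomes {18a}), and a journal article leaves operational scoring rules to the full protocol.

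Much of this stands as evidence of intent: the emergencies were very probably meant to count. It does not change the definition. Training passes on the written rule and does not rewrite it. Nor is this a detail left out for brevity: the article states the rule, and the rule as stated gives the wrong score.

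The apnea criterion gives only partial support. It counts "three or more apnea events requiring intervention (stimulation, increasing oxygen or ventilation pressure) within one hour", which in part presumes room to go up. But stimulation is possible at the ceilings, as is the bag-mask ventilation in the same criterion, so a reader should not infer that this criterion cannot be met there.

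**Conclusion.** The point holds as a fault in the wording of the primary outcome. It assumes that maximal therapy means the stated ceilings, which is a natural reading but not the only one. On that reading, emergency intubations below the ceilings within 72 h are not treatment failures, against the objective and the stopping rule.

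Its size cannot be derived. The protocol does not say how often such intubations occur, and the planning rates come from a trial that is also cited for this outcome and may already carry the same condition.

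A reader might go further and infer a bias toward one arm, because the ceilings differ by mode and staff are unblinded. A reader might also infer a loss of power from unscored failures. The documents support neither: they give no difference between arms, and any power figure would rest on an invented share of unscored failures. Nor do they show that such infants will in practice be mis-scored, given the likely intent. The correction is still worth making, because it is specific and cheap and it concerns the primary outcome.

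**What to change.** Add to the outcome definition that the maximal-therapy condition does not apply to emergency intubation under the fourth criterion: any such intubation within 72 h of randomization is a treatment failure whatever the settings. Exclude the brief intubation for surfactant, since under Weaning from study interventions "A dose of 200 mg/kg will be administered by INSURE (intubation-surfactant-extubation) method". Apply the rule to all infants, including those already enrolled. The first three criteria stay as they are, and no sensitivity analysis is required.

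The cost is a short clarification. Recruitment began on September 1, 2023 (Trial status), and the change bears on the evaluation of results, so the protocol's own amendment section {25} calls for ethics notification and a registry update. The observed failure rate may be slightly higher than under the literal wording.
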